### Practice characteristics

To measure organizational readiness, we use the 24-item Organizational Change Recipients’ Beliefs Scale (OCRBS). Response options ranged from 1 (*Strongly disagree*) to 5 (*Strongly agree*) [39].

### Barriers and facilitators to implementation and sustainability

Qualitative interviews explore the implementation process and the potential for sustainability guided by CFIR. In a purposive sample of eight sites per wave, two staff members per site are selected to participate in an interview six months after the end of the intervention. The interviews explore specific elements of the transformation processes to achieve TBC and HTN management and outcome goals, team member experiences with TBC, how various challenges were identified and addressed, satisfaction with the PF process, and strategies for sustaining gains.

In addition, qualitative interviews will be conducted with the practice facilitators at 12 months to further assess the implementation process, including contextual facilitation barriers, and facilitators that influenced TBC implementation, review adaptations to components and of TBC, what worked/did not work, and recommendations for enhancing sustainability and scale up. Informed consent will be obtained from all subjects. All study participants will receive an email describing the study with a link to the survey; the landing page will include the consent form, and clicking the link will indicate consent. Lead clinicians and other staff members invited to participate in qualitative interviews will be asked to provide verbal consent. Those who complete the interview will receive a $50 gift card as compensation. The study protocol was reviewed and approved by the New York University Institutional Review Board.

### Analysis

#### Quantitative analysis

The primary outcome is the overall average score on the TBC assessment tool. The secondary outcome is patient BP control. The analysis of the effect of PF on the TBC adoption outcome measure will be based on a linear mixed model. Specifically, to assess the PF intervention effect compared to usual care, we will use a model with a random site effect, and fixed effects for time and study condition. Condition will be dummy coded with the control condition as a reference category. The fixed-effects coefficient for the contrast of the PF condition with the control condition will indicate the direction and magnitude of the difference on the overall average TBC score. Inclusion of a fixed effect for time accounts for any general time trends. We also will explore whether the time coefficient should have a random effect to capture differences in time trends across practice sites. Confidence intervals (95%) will be reported to convey precision. In addition to the effects of time and condition, covariates (e.g., organizational readiness) will be considered for inclusion in the mixed-effects model to reduce the within-group variance, if the potential covariate is predictive of the outcome.

For the BP secondary outcome, a generalized linear mixed model will be used. The count of HTN patients with BP control (< 140/90) will be regressed on fixed effects for time and condition, the natural logarithm of the total number of HTN patients as an offset, and a random site effect. For the count outcome, a Poisson model will be used, but we also will consider a negative binomial mixed model if overdispersion is found. The offset term allows us to model the *rate* of BP control in each practice site and adjusts for differences in the number of HTN patients across sites. Comparisons of conditions (e.g., PF vs. control) can be converted to incidence rate ratios (IRRs) by exponentiating the appropriate fixed-effects coefficient or contrast.

Models will be fit using the *glmmTMB* package using R software [51, 52]. Each of the PF intervention effects will be tested using a two-sided level of significance α = 0.05. For the blood pressure secondary outcome, we will also conduct sub-analyses to assess outcomes by race/ethnicity.

Potential moderator effects will be examined by including separately each organizational characteristic as a main effect and in interaction with the treatment condition indicator (Control vs. PF vs. Sustainability). A significant interaction effect would indicate the effect of the condition depends on the moderator, and contrasts of the control and PF periods at different levels of the moderator would be undertaken to understand the pattern of the interaction. We will conduct further analysis to explore the possibility that changes in organizational readiness mediate the effect of PF on primary and secondary outcomes. We will conduct preliminary analyses to assess whether PF (versus Control) is associated with changes at the site level. If there is a detectable effect of the PF intervention on these measures, we will assess whether the changes in these measures are associated with changes in overall average TBC and HTN management scores and changes in the rate of BP control using the Baron and Kenny “product method” as a starting point of the analysis [53]. If necessary, we will explore more complex structural equation models (SEM) adapted for Poisson outcomes [54] as well as more recently developed causal inference methods [55, 56] to evaluate the mediation.

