#### Power analysis

With the pre-specified number of sites (90) and design (Table 1; stepped-wedge design with 3 waves and 6 time periods; n = 432 TBC overall average scores), we investigated the PF intervention effect that is detectable with at least 80% power of a 2-sided significance test with α = 0.05. Power was calculated by simulating ten thousand datasets with modest correlation of TBC overall average scores over time (*r* = 0.35; ICC = 0.32) [57], and a standardized mean difference between control and PF conditions of *d* = 0.5 (i.e., a difference of half a standard deviation). Power was 0.92 to detect this effect with the planned number of sites. To allow for withdrawal of a small number of sites after baseline, we plan to enroll 90 practice sites (30 in each wave). Power for the secondary blood pressure outcome was also calculated by simulating ten thousand datasets. In all conditions, we assume an average of 150 patients with HTN per site and time period (i.e., 64,800 observations of patient BP over all sites and time periods). The intraclass correlation for BP control was specified as ICC = 0.85 based on an estimate from our previous EvidenceNOW study [25]. For the control condition, we specified a rate of BP control of 70%. For the PF condition, we specified an increase in the rate of BP control to 75%, and for the follow-up condition, we specified a decrease to 72%. The difference between the control and PF conditions corresponds to IRR = 1.07. Power to detect this IRR was > 0.99.

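### The time term reads as one linear slope, which cannot remove every calendar trend as claimed, and the stated TBC power of 0.92 on 432 scores fits a slope but not six period effects

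*Protocol article*

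**What the plan says.** Under Quantitative analysis, the TBC model is described as follows: "we will use a model with a random site effect, and fixed effects for time and study condition". The role of the time term is then stated: "Inclusion of a fixed effect for time accounts for any general time trends". The next sentence adds: "We also will explore whether the time coefficient should have a random effect to capture differences in time trends across practice sites". The BP count "will be regressed on fixed effects for time and condition", with an offset and a random site effect, in a Poisson model.

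The coding of condition is explicit: "Condition will be dummy coded with the control condition as a reference category". Later in the same section it has three levels: "treatment condition indicator (Control vs. PF vs. Sustainability". No such statement is made for time.

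Under Power analysis, the layout is a "stepped-wedge design with 3 waves and 6 time periods; n = 432 TBC overall average scores", with d = 0.5, r = 0.35 and ICC = 0.32. The result is: "Power was 0.92 to detect this effect with the planned number of sites".

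**The concern.** In a stepped wedge, later calendar periods contain more PF exposure, so the time term is the main protection against confounding by calendar change. Six-level time has five contrasts and no single coefficient. One coefficient that may be given a random effect, so that trends differ between sites, is a slope.

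If a slope is what will be fitted, the sentence on general time trends is wrong. Curved, stepped or seasonal change is then partly attributed to PF, and the confidence interval does not show it. If period effects are intended, the sentence is sound for change common to all sites, but 0.92 looks too high for 432 scores. Either way one statement in the article needs correcting.

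**Working it through.** **Inputs.** From Study design: 6-month steps and 12 months of PF. From Quantitative analysis: three conditions and a random site effect. From Power analysis: 3 waves, 6 periods, n = 432, d = 0.5, correlation 0.32 or 0.35, two-sided α = 0.05, stated power 0.92. The number of sites implied is 432/6 = 72, or 24 per wave. The BP figures agree: 64,800/150 = 432 site-periods.

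**Assumed layout** (C control, P facilitation, S sustainability): wave 1 C P P S S S; wave 2 C C P P S S; wave 3 C C C P P S.

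**Formula.** With total SD 1 and V = (1 - ρ)I + ρJ within site, the covariance of the fixed effects is [Σ n_w X_w'V⁻¹X_w]⁻¹. SE is the root of the PF entry, and power = Φ(0.5/SE - 1.96).

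**Step 1: TBC power.** Ranges run from ρ = 0.32 to 0.35.

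| Layout | Time term | SE | Power |
|---|---|---|---|
| 72 x 6 = 432 | linear | 0.151 to 0.149 | 0.911 to 0.919 |
| 72 x 6 = 432 | quadratic | 0.162 to 0.159 | 0.870 to 0.881 |
| 72 x 6 = 432 | six periods | 0.166 to 0.163 | 0.855 to 0.866 |
| 90 x 6 = 540 | six periods | 0.148 to 0.146 | 0.921 to 0.929 |

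Simulation of the 72 x 6 layout (2,000 datasets per setting) gave 0.919 to 0.926 for linear time and 0.856 to 0.866 for six periods. A layout that stops each wave at 18 months averages five scores per site. Scaled to 432 scores it needs 432/5 = 86.4 sites, and six periods then give 0.891 to 0.899.

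**Step 2: leakage for BP** (all sites, all six periods, no true PF effect). A calendar pattern f is passed through the linear-time estimator: bias = PF entry of [Σ n_w X_w'V⁻¹X_w]⁻¹ Σ n_w X_w'V⁻¹f. Ranges cover ρ from 0.32 to the plan's BP value of 0.85.

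- Step after the first period: +0.15 to +0.17 of its size.
- Rise that levels off at month 12: +0.19 to +0.20.
- Rise that starts after month 12: -0.13.
- Straight line: 0.

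With six period effects every value is 0. For assumed calendar changes of 3 to 5 points, the bias runs from 3 x 0.13 = 0.4 to 5 x 0.20 = 1.0 points in absolute size. That is 8% to 20% of the planned 5-point difference (70% to 75%). Other shapes leak more or less than this.

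**Step 3: SE cost for BP.** With residual variance 0.21/150 per site-period, ICC 0.85 and 72 sites, SE rises from 0.73 to 0.80 points (0.80/0.73 = 1.09). Since 5/0.80 = 6.2, power stays above 0.99. If Poisson SEs are used (about 1.31 points with linear time, 1.31 x 1.09 = 1.43 with periods), the estimate must exceed 1.96 x 1.43 = 2.80. Power is then Φ((5 - 2.80)/0.80) = Φ(2.75), still above 0.99.

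**Step 4: TBC as collected** (before the start, at 12 months and at 18 months). The layout becomes wave 1 C . P S . . ; wave 2 . C . P S . ; wave 3 . . C . P S. With six-level time, the GLS weights for the PF effect are +1 on wave 1 at 12 months, -1 on wave 3 at baseline, and 0 elsewhere, whatever ρ is.

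- 72 sites: SE = √(2/24) = 0.289, power Φ(0.5/0.289 - 1.96) = 0.41. Linear time gives about 0.50.
- 90 sites: SE = √(2/30) = 0.258, power 0.49. Linear time gives about 0.59.

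**The case against.** **The coding is not stated.** Fixed effects for time can mean categorical periods, the phrase about a single coefficient occurs only in an exploratory remark, and a condensed article may leave coding to a fuller plan. This stands against saying that the plan specifies a slope. It does not rescue the article's own claim about general time trends, which is true only for one of the two codings.

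**The power match is not proof.** The Power analysis names 90 sites as well as 432 scores, and 90 x 6 with six periods also gives 0.92. This stands in part. That layout has 540 scores, however, while both 432 and 64,800/150 point to 72 x 6. The coding used in a power simulation also need not be the coding of the final analysis.

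**Type I error.** A reader might infer a badly inflated error rate for BP. With binomial-type SEs (0.71 points), a 3-point step would give about 10% and a 5-point plateau about 29%. The planned model is Poisson, and its SE in this setting is about 1.31 points against a true 0.73, so the threshold is 1.96 x 1.31 = 2.57. The step gives a bias of 3 x 0.154 = 0.46 and (2.57 - 0.46)/0.73 = 2.89, or 0.2% rejection. The plateau gives 5 x 0.192 = 0.96 and 2.21, or 1.4%. The inflation claim therefore fails under the planned model. The bias remains.

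**Six periods serve TBC badly on the collected schedule.** This stands: Step 4 shows that the estimate would ignore wave 2 and every within-site change.

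**Conclusion.** The point holds as a mismatch between what the article claims, what its wording suggests and what its power figure fits. The claim to account for any general time trend is too strong for a single slope. On 432 = 72 x 6 scores, 0.92 fits linear time and is 5 to 6 points above the result for six period effects. For BP the consequence is a bias of roughly 0.4 to 1.0 points for calendar steps, plateaus or late rises of 3 to 5 points.

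This rests on three assumptions: an inferred layout, an inferred coding, and calendar changes whose size and shape the article does not give. A reader might infer that the trial is underpowered because of the time coding. The documents do not support that: on the stated layout power with period effects stays above the 80% target. The much lower TBC figures in Step 4 come mainly from the gap between six scores per site and the three that are collected.

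**What to change.** - **BP model:** state that time is a six-level categorical period effect, and keep linear time as a sensitivity analysis. Cost: an SE about 9% larger, with power still above 0.99 on the planned effect.
- **Sentence on time trends:** correct it to match the coding. With period effects it can claim to remove calendar change that is common to all sites. With a slope it can claim only a linear trend.
- **TBC model:** first reconcile the six-score layout in Power analysis with the collection times in Study design and Primary outcome, then name the coding. Six-level time should not be adopted by default, because on the baseline, 12- and 18-month schedule it lowers power from about 0.50 to 0.41 (72 sites) or from 0.59 to 0.49 (90 sites).
- **TBC power:** restate it under the coding and layout actually used, with the number of sites and scores made consistent. On 72 x 6 with period effects it is about 0.86.

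The cost is a few sentences and one rerun of the simulation.

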#### Secondary outcome

We assess the percentage of patients with BP < 140/90 [48]. Data on BP is obtained through the EHR. Using the National Quality Forum-endorsed BP control measure [48], the denominator is defined as the count of all individuals, ages 18–85, with a diagnosis of HTN, who were seen at least once during the measurement period. The numerator represents the count of individuals who met the denominator criteria whose latest measured BP in the measurement period was less than 140/90 [49]. We obtain reports on BP control at baseline, and every six months thereafter, coinciding with the stepped-wedge design, using the most recent prior 6-month measurement period. BP data is extracted from the EHR systems through existing reporting and registry tools. We also collect aggregated data on race/ethnicity and insurance status among patients with HTN.

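### BP control is a proportion of about 70–75% but is modelled as a Poisson count with only an overdispersion check, so its standard errors can be up to about 1.8 to 2 times too large

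*Protocol article*

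**What the plan says.** All references are to the protocol article.

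- **Secondary outcome.** The denominator is every adult aged 18–85 with hypertension seen in the period. The numerator is a subset of it: "The numerator represents the count of individuals who met the denominator criteria whose latest measured BP in the measurement period was less than 140/90". Each patient contributes one yes or no, so the outcome is y out of a known n.
- **Quantitative analysis.** The count of controlled patients is regressed on time and condition, with "the natural logarithm of the total number of HTN patients as an offset, and a random site effect". The distribution is fixed as follows: "For the count outcome, a Poisson model will be used, but we also will consider a negative binomial mixed model if overdispersion is found". Effects are "tested using a two-sided level of significance α = 0.05". No binomial model, robust variance or provision for underdispersion is given for BP.
- **Power analysis.** "For the control condition, we specified a rate of BP control of 70" per cent, with 75% under facilitation and 72% at follow-up, an average of 150 patients per site and period, and 64,800 observations in all. On the between-site correlation: "The intraclass correlation for BP control was specified as ICC = 0.85 based on an estimate from our previous EvidenceNOW study". The result: "Power to detect this IRR was > 0.99".

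**The concern.** A Poisson model with a log-denominator offset is a good stand-in for a binomial only when the event is rare. At 70% it is not rare: the model credits each site-period count with far more random variation than y out of n can have. The data are then underdispersed relative to the model, and the only diagnostic named looks in the other direction.

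At stake are the confidence intervals and p-values for the trial's clinical outcome. They feed the sub-analyses by race/ethnicity and the moderator analyses of the BP outcome, where effects may be smaller and information thinner. Real variation between periods within a site can also go unnoticed, because it is absorbed in the surplus Poisson variance instead of being estimated.

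**Working it through.** **Inputs from the document.** Control 70%, facilitation 75%, follow-up 72%; n = 150 per site-period; 64,800/150 = 432 site-periods = 72 sites × 6 periods; ICC 0.85; two-sided α = 0.05.

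**Assumptions.** Table 1 is not shown, so the schedule was built from the text (waves 6 months apart, 12 months of facilitation): wave 1 C, PF, PF, S, S, S; wave 2 C, C, PF, PF, S, S; wave 3 C, C, C, PF, PF, S. The ICC was read as the between-site share of variance in site-period rates: 0.7 × 0.3/150 = 0.0014; 0.0014 × 0.85/0.15 = 0.0079; site SD about 0.089. There were 24 sites per wave.

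**1. The plan's own figure.** IRR = 0.75/0.70 = 1.071. Binomial data fitted with the planned Poisson random-site model gave power 0.997 (300 runs). This agrees with the stated figure.

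**2. Variance functions.** For a count with n = 150 and p = 0.70:
- Poisson: np = 105.
- Binomial: np(1−p) = 31.5.
- Ratio 105/31.5 = 1/(1−p) = 3.33, so the SE ratio is 1/√(1−p): 1.83 at 70%, 1.89 at 72%, 2.00 at 75%.

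**3. In the planned design.** Generalised least squares gives an SE for the facilitation log rate ratio of about 0.020 (Poisson) against 0.011 (binomial), a ratio of 1.86–1.89. The ratio is the same at 72 and 90 sites. In the simulation at 70/75/72% the mean model SE was 0.0202 against an empirical SD of 0.0111, a ratio of 1.82.

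**4. Adding site-by-period variation.** With SD s on the proportion scale, the count variance is about 31.5 + (150s)², and the expected SE ratio is √(105/that). Simulated values are under no effect at 70% (600 runs in the first row, 200 in the others, so ratios in those carry about 5% Monte Carlo error).

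| s (points) | Count variance | Expected SE ratio | Simulated SE ratio | Rejections at nominal 5% | Pearson dispersion |
|---|---|---|---|---|---|
| 0 | 31.5 | 1.83 | 1.77 | 0 of 600 | 0.33 |
| 2 | 40.5 | 1.61 | 1.51 | 0% | 0.41 |
| 3 | 51.75 | 1.42 | 1.37 | 1.5% | 0.53 |
| 4.5 | 77.1 | 1.17 | 1.20 | 2.5% | 0.77 |
| 6 | 112.5 | 0.97 | 0.89 | 9.5% | 1.11 |
| 8 | 175.5 | 0.77 | 0.81 | 15% | 1.72 |

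Break-even: (150s)² = 105 − 31.5 = 73.5, so s = 0.057, or 5.7 points. A separate simulation with 90 sites gave SE 0.0189 against SD 0.0101 (ratio 1.87) and test size 0.2% with no extra variation, and a ratio of 1.5 at 3 points.

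**5. The fallback.** Negative binomial variance is μ + μ²/θ, never below μ, so it cannot correct rows where dispersion is below 1. At 3 points the true variance is 51.75/31.5 = 1.64 times binomial, yet dispersion against Poisson is 0.53: the check finds nothing.

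**6. Smallest effect detectable with 80% power (72 sites, no extra variation).**
- Binomial data, Poisson SE: 1.96 × 0.0202 + 0.84 × 0.0111 = 0.0489, so a ratio of 1.050 (70% to 73.5%).
- Correct binomial SE: 2.80 × 0.0109 = 0.0305, so a ratio of 1.031 (70% to 72.2%).

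**The case against.** **The error is conservative and the outcome secondary.** With little site-by-period variation, false positives are not inflated and the planned contrast keeps power of 0.997. This stands and limits the severity.

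**The direction is not known.** It turns on a site-by-period SD that the document does not give. A value of zero is unlikely for small practices reporting from EHR extracts, so 1.8 lies at one end of a range. This also stands. It does not rescue the model: its standard error is right only when that SD happens to be near 5 to 6 points.

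**The fallback is reasonable.** It is invoked only if dispersion exceeds Poisson, where wider intervals are appropriate. That is correct for the last rows of the table, but it does nothing for the others.

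**The IRR is already a ratio of proportions.** With a log link and log-denominator offset this is true; the estimand is not at fault, only its error bars.

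**Two stronger readings are tempting, and the document supports neither.**
- A reader might infer that the stated power is wrong, because counts drawn from a Poisson distribution give about 0.92–0.93 analytically at 72 sites. The article does not say that counts were drawn that way, and binomial draws reproduce its figure.
- A reader might infer that an ICC of 0.85 is impossible, given that eligible practices have under 75% control. The article does not place that ICC on the patient scale. The 75% limit is an entry screen, not a bound in every period, and reading the ICC as a share of variance in site-period rates gives a workable site SD.

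**Conclusion.** The concern holds. The planned variance function does not suit a proportion of 70–75%, and the only check named cannot detect or repair underdispersion.

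- **Size.** Standard errors are about 1.8 times too large at 70% (2.0 at 75%) if within-site variation is purely binomial, with test size well under 1%. The factor is about 1.4 at a site-by-period SD of 3 points and 1 near 5 to 6 points. Beyond that the Poisson standard error is too small.
- **Consequence.** BP confidence intervals of the wrong width and reduced sensitivity to effects smaller than 70% to 75%. Loss in the race/ethnicity and moderator analyses is probable but was not quantified.
- **What it rests on.** The variance ratio needs only the document's definition and assumed rates. The simulated figures also rest on the reconstructed schedule, 150 patients per site-period and the reading of the ICC above.

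This should be corrected before analysis. It is not critical, because BP control is secondary and the main contrast keeps its power.

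**What to change.** In Quantitative analysis, replace the Poisson/negative binomial model for BP control with one of the following, fitted to controlled and not-controlled counts:

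- a beta-binomial mixed model with a random site effect; or
- a binomial (logit) mixed model with random site and random site-by-period intercepts.

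Keep the fixed effects for time and condition. Do not use a plain binomial with a site intercept only: at a 3-point site-by-period SD its standard error would be √(31.5/51.75) = 0.78 of what it should be, and its simulated test size was 11.5%. Report a risk ratio and a risk difference by standardisation.

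**Cost.** A change of wording, with the same counts and the same glmmTMB software. Analysis work rises slightly, and the ratio of proportions has to be obtained by standardisation instead of being read from the coefficient.

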### Conceptual framework

The study design and assessments are informed by principles of TBC, and Armenakis’s theory of organizational readiness [39]. Armenakis’s theory posits that successful implementation of a change effort is determined by the extent to which the change recipient perceives a need for change, is confident in their ability to change, believes there is commitment from formal and opinion leaders, believes a change will be beneficial, and believes that the change is appropriate.

We hypothesize that additional organizational features (e.g., staffing, resources) will moderate the effectiveness of PF (Fig. 1). We further hypothesize that PF will increase the adoption of TBC principles and HTN management strategies by increasing organizational readiness (e.g., clinician efficacy and motivation to implement the practice changes necessary to improve HTN outcomes) [39, 40]. Qualitative assessment of the contextual barriers to and facilitators of implementing TBC for improving HTN management will be further guided by the Consolidated Framework for Implementation Research (CFIR) [41]. The CFIR broadens the inquiry by capturing additional organizational, individual, and intervention characteristics that may impact implementation effectiveness and sustainability and the process by which practice change is achieved, including the role of practice facilitators as change agents.

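### The moderator models have no characteristic-by-time term, so a background trend that differs by an organizational characteristic biases the interaction and can be read as moderation of practice facilitation

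*Protocol article*

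**What the plan says.** The Conceptual framework section hypothesizes that "additional organizational features (e.g., staffing, resources) will moderate the effectiveness of PF". The Quantitative analysis section tests this by "including separately each organizational characteristic as a main effect and in interaction with the treatment condition indicator (Control vs. PF vs. Sustainability", and fixes the reading of the result: "A significant interaction effect would indicate the effect of the condition depends on the moderator". A significant interaction is then followed by Control-versus-PF contrasts at different levels of the moderator.

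These terms are added to the base models of the same section. For TBC, "we will use a model with a random site effect, and fixed effects for time and study condition". The purpose of the time term is stated: "Inclusion of a fixed effect for time accounts for any general time trends". One further sentence in the TBC paragraph bears on trends: "We also will explore whether the time coefficient should have a random effect to capture differences in time trends across practice sites". For blood pressure (BP), the count of controlled patients "will be regressed on fixed effects for time and condition, the natural logarithm of the total number of HTN patients as an offset", with a random site effect. The BP paragraph mentions no random time effect.

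**The concern.** The null hypothesis of interest is that the PF effect is the same at every level of the characteristic. The stated model tests something narrower: no moderation and also the same background trend at every level. In a stepped wedge, later calendar time means more PF and more Sustainability. If better-staffed or better-resourced practices improve at a different rate anyway, the only terms that can absorb the difference are characteristic-by-PF and characteristic-by-Sustainability. The staggered start separates condition from the common trend, because time is in the model. It cannot separate characteristic-by-condition from characteristic-by-time when the latter is left out.

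At stake is the answer to which practices PF works better in. The plan's rule could report moderation when PF has the same effect everywhere.

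**Working it through.** **Inputs from the Protocol article.** 90 sites, 30 per wave; three waves, six periods, 6-month steps, 12 months of PF; r = 0.35 and ICC = 0.32 for TBC; planned effect 0.5 SD; two-sided α = 0.05.

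**Assumptions.** Table 1 is not shown, so the layout is inferred from the Study design section: wave 1 = C,PF,PF,S,S,S; wave 2 = C,C,PF,PF,S,S; wave 3 = C,C,C,PF,PF,S. The moderator has two equal-sized levels, balanced over waves. True moderation is zero. The background trend differs between levels by g SD per 6 months. The documents do not give g, so a range is shown.

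**The plan's own power first.** With a random site intercept and generalized least squares (GLS), power = Φ(0.5/SE − 1.96).

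- 432 scores (72 × 6), linear time, ICC 0.32: SE 0.151, power 0.911 (0.919 at 0.35).
- 540 scores (90 × 6), categorical time, ICC 0.32: SE 0.148, power 0.921.
- 432 scores, categorical time, ICC 0.32: SE 0.166, power 0.855.

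The stated 0.92 is reproduced by the first two, so the set-up is adequate. It does not settle how many TBC scores each site gives. The Power analysis section counts 432 over six periods, while the Study design and Primary outcome sections describe baseline, 12 and 18 months, which is 90 × 3 = 270. Both layouts are carried through.

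**Size of the bias.** With three scores, PF is always measured two periods after Control, so the false characteristic-by-PF coefficient is exactly 2g. With six scores, the mean PF period minus the mean Control period is 2.5 − 1 = 1.5, 3.5 − 1.5 = 2 and 4.5 − 2 = 2.5 in waves 1 to 3. The average is again 2, and the exact GLS expectation is 2g to within rounding. The bias is the 12-month trend difference.

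**Rejection rate.** With z = 2g/SE, P(reject) = Φ(−1.96 − z) + 1 − Φ(1.96 − z), for the 1-df characteristic-by-PF test with 90 sites:

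| g (SD per 6 months) | False estimate (SD) | Three scores, r = 0.35, SE 0.240 | Six scores, ICC 0.32, SE 0.176 |
|---|---|---|---|
| 0 | 0 | 5% | 5% |
| 0.05 | 0.10 | 7% | 9% |
| 0.10 | 0.20 | 13% | 21% |
| 0.15 | 0.30 | 24% | 40% |
| 0.20 | 0.40 | 38% | 62% |

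The 2-df test over Control, PF and Sustainability rejects more often. At g = 0.10 it rejects in 19% (three scores) or 49% (six scores).

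**Random time slope.** At g = 0.10 with six scores, slope variances of 0.001, 0.01 and 0.05 leave 0.199, 0.192 and 0.166 of the 0.200 SD bias. With three scores, a variance of 0.01 leaves 0.198. Random slopes are centred on one common mean slope, so they widen the standard error more than they move the estimate.

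**With characteristic-by-time added.** The false estimate is 0 and rejection is 5% for linear or categorical coding, and the model has full rank. The standard error becomes:

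- three scores: 0.240 to 0.457 (linear, 1.9-fold) or 0.516 (categorical, 2.2-fold);
- six scores: 0.176 to 0.270 (1.5-fold) or 0.296 (1.7-fold).

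**BP.** The mechanism is the same. As an assumed illustration, a trend difference of 1 percentage point per 6 months gives a false interaction of about 2 points. From the planned 70% control rate, that is a ratio of rate ratios of about 72/70 = 1.03. No false-positive rate is put on BP here.

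**The case against.** **The plan allows for site-specific trends.** A reader might infer that every practice is forced onto one time trend. The documents do not support that for TBC, where a random time effect will be explored. This limits the wording, but the random effect is exploratory, is named only for TBC, and leaves most of the bias.

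**Not every trend difference would be declared moderation.** That too is a tempting reading, and it is too strong. At 0.05 SD per 6 months the three-score test rejects in 7%, and at 0.10 SD it stays silent 87% of the time. The coefficient is biased throughout, but a false claim depends on the size of the difference.

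**The size is assumed.** This stands. The top of the range, 0.20 SD per 6 months, is 0.40 SD over 12 months, or 80% of the planned 0.5 SD effect.

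**The 2-df figures overstate the harm.** Largely accepted. The plan follows a significant interaction with Control-versus-PF contrasts, so the 1-df figures are the relevant ones.

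**The remedy trades bias for variance.** With three scores, the current model's root mean squared error is √(0.240² + 0.20²) = 0.31 at g = 0.10 and √(0.240² + 0.40²) = 0.47 at g = 0.20, against 0.46 or 0.52 after the fix. With six scores it is √(0.176² + 0.20²) = 0.27 at g = 0.10, level with 0.27 (linear) and below 0.30 (categorical). The fix therefore does not always give a closer estimate. It does restore the validity of a test that the plan uses to assert moderation, and reporting both models shows the trade.

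**The analyses are secondary, and an article condenses.** The first part is true and limits the weight of the point. On the second, this article names the model terms and the inference rule, so the point concerns stated text.

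**Conclusion.** The concern holds in a limited form. As written, the moderator models cannot distinguish a PF effect that depends on the characteristic from a background trend that does, and the rule that a significant interaction indicates moderation does not follow. The bias is about the 12-month trend difference. The false-positive rate is 5% if trends are equal and roughly 7% to 38% (three scores per site) or 9% to 62% (six) over the assumed TBC range. These figures rest on the inferred layout, an even two-level moderator and an assumed trend difference.

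Two further inferences are not supported. The main PF analyses are not compromised, because they contain no interaction and adjust for the common trend. Nor do the documents show that BP should carry the moderator inference because TBC has too few scores. The number of TBC scores per site is unclear, and the precision cost differs between the two readings. The change should be made, but it does not threaten the primary result.

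**What to change.** In the moderator paragraph of the Quantitative analysis section:

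1. Fit each moderator model, for TBC and BP, with a characteristic-by-time term, coded as time is in the main model.
2. Base any claim that a characteristic moderates PF on the 1-df characteristic-by-(PF vs Control) contrast from that model, with its 95% CI.
3. Report the model without the term alongside, labelled as the version that assumes equal trends.

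This needs one extra model term, a sentence or two of text and no new data. The price is precision: the TBC interaction standard error rises about 1.5 to 1.7-fold with six scores per site, or about 1.9 to 2.2-fold with three. TBC moderator results should therefore be presented as estimates with intervals. The narrower intervals of the present model come from assuming equal trends.
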